D. When each institution confirms that eligible subjects are hospitalized as planned and there is no change to the eligibility (change of surgery method, etc.), the institution shall notify KGOG accordingly and request randomization. KGOG will access the eCRF System (Redcap), input the data on the eligibility sheet and perform randomization. Random numbers will be assigned in the form of ‘R_XX_01’ where XX is the initials of the institutions.

D. Randomization table is created in advance and embedded in the eCRF system. The randomization table is created in advance by the Medical Research Cooperation Center of Seoul National University Bundang Hospital and will be imported to the eCRF system directly without the involvement of investigators. Details of the randomization table are as follows:

A) The ratio of SS-PDS experimental group vs. control group is 1:1

B) The ratio of subcutaneous drainage experimental group vs. control group is 1:1

C) Stratification factors are institutions and BMI (≤30 vs >30), Surgery indication (Confirmed or suspected cancer vs not). The Stratification factors are applied to all of A), B), and random.

D) Block randomization

(5) Notification of randomization results

A. Randomization results should not be notified until just before the fascia closure begins during surgery.

B. Just before the fascia closure begins, each institution will notify the screening number to KGOG by phone and check the randomization result by phone as well.

C. Randomization results will not be notified using numbers such as 0 or 1 but in the form of ‘SS-PDS experimental group’ or ‘subcutaneous drain control group.’ After being notified of the randomization results, each institution will say out the result again to KGOG so as to avoid any error.

D. KGOG will create a record on the eCRF according to random number and inform the pair of screening number-randomization number to each institution so that the institution can input data on the eCRF.

(6) Nondisclosure of randomization results

A. SS-PDS randomization results

A) Study subjects are not notified of the randomization results.

B) In order to minimize investigator influence on the randomization at the time of incisional hernia diagnosis, randomization results are not recoded on medical records but only on CRF.

B. Subcutaneous drain randomization results

Randomization results are disclosed

(7) Undisclosed randomization results are disclosed to:

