A. investigators: investigators at each institution can view CRF and check randomization results without a separate approval procedure.

B. study subjects: if investigators see it necessary for medical purposes, they can inform the subjects of the randomization results after approval by the principal investigator.

(8) Interim Analysis

A. Interim analysis for the initial safety review

A) When the 10th subject is allocated to A+B arm and finishes his/her Week 4 visit, an evaluation will be performed on 10 subjects in A+B arm for incidence, types, and grades of surgical site infections, wound dehiscence, and other adverse events.

B) Evaluation results will be reported to IRB. If incidence, types, and grades of adverse events are judged to exceed the usual range, possible measures including trial discontinuation will be considered.

B. Interim analysis for wound dehiscence of subcutaneous drain

A) An evaluation will be performed when the 44th subject of A+C arm and B+D arm, respectively, completes his/her week 4 visit.

B) If wound dehiscence incidence of A+C arm is lower than B+D arm (one-sided p < 0.005), it will be decided that subcutaneous drain insertion reduces wound dehiscence and further randomization will be stopped. That is to say that subcutaneous drain will be inserted to all subject from then.

1. **Investigational Product Dosage, Application/Administration Methods, Combination Therapy, and Reasons for Comparator (as applicable)**

(1) SS-PDS arm (fascia closure using SS-PDS)

A. Instructions

A) STRATAFIX Symmetric PDS Plus, suture size: 1/0, suture length: 45cm, needle size: 40mm (CT needle) (Ethicon, Somerville, NJ, USA)

B) Running suture will be used as recommended by the manufacturer and stated in previous studies [PMID: 28603661] (<https://www.youtube.com/watch?v=PTYtYvSaGMg>, <https://youtu.be/TPyulS4fQgQ>)

C) Peritoneum closure should be performed. If peritoneum closure is impossible due to peritoneotomy, it may not be performed.

D) For fascia closure, stiches will be made 5-8 mm apart including 5-8 mm thick tissues on both sides of the incision surface.

E) It is allowed to make additional stiches for fascia closure with a few interrupted sutures using PDS or other sutures based on the investigator’s judgment.

F) Suture length is recommended to be 4 times longer than the skin incision. That is, if the skin incision is 20cm, it is recommended to use 80cm or longer suture for closure.

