2. Subcutaneous tissue closure is not necessary, but can be performed based on the investigator’s judgment.

3. Skin closure can be performed using stapler or non-absorbent sutures whichever is a general method of each institution.

B. Reasons for the choice

The reasons are stated under the section ‘Background.’

1. **Observation Items, Clinical Test Items, Observation and Test Methods**

| Observation Items | Observation and Test Methods |
| --- | --- |
| 1-year cumulative incidence of incisional hernia after surgery | Subjects are advised to make outpatient visits for Year 1 after surgery. Visits made between 9 and 15 months after surgery can be counted as Year 1 visit. Investigators will conduct a physical checkup to diagnose incisional hernia. Investigators can refer to post-surgery image test result. If investigators are not sure of incisional hernia, a diagnostic test can be carried out. Subjects will be censored if they underwent midline laparotomy once again after receiving the surgery from this study, are dead or lost to follow-up at the time of event. Investigators will not be reminded of group allocation and will be blinded until Year 1 visit is completed. |
| 4-week cumulative incidence and types of surgical site infection after surgery | Subjects are advised to make outpatient visits for Week 4 after surgery. Visits made between 3 to 5 weeks after surgery can be counted as Week 4 visit. Investigators will conduct a physical checkup to diagnose surgical site infection. If subjects make outpatient visits before Week 4 after surgery, investigators should check for surgical site infections and their types. All information obtained from visits made immediately after surgery up to Week 4 will be used to diagnose all surgical site infections. CDC standards will be used to determine surgical site infections and their types. (https://www.cdc.gov/nhsn/PDFs/pscManual/17pscNosInfDef_current.pdf). If any surgical site infection is observed according to CDC standards, the patient will be judged to have a surgical site infection. Investigators will not be reminded of group allocation. |

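### The blinding of hernia assessors until Year 1 is stated but not secured, because site investigators may look up the suture allocation in the CRF without approval

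*Protocol*

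**What the plan says.** Four parts of the protocol bear on who knows the suture allocation when hernia is judged.

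- **Observation items, 1-year hernia incidence.** "Investigators will conduct a physical checkup to diagnose incisional hernia". Imaging is optional: "Investigators can refer to post-surgery image test result". A further test is possible if the investigator is unsure. On blinding, the row states: "Investigators will not be reminded of group allocation and will be blinded until Year 1 visit is completed".
- **Control Group Setting and Randomization, item (6) A.** Subjects are not told the SS-PDS result. To limit investigator influence when hernia is diagnosed, "randomization results are not recoded on medical records but only on CRF". The drain allocation is open (item (6) B).
- **Same section, item (7).** Under the lead-in "Undisclosed randomization results are disclosed to", part A provides that "investigators at each institution can view CRF and check randomization results without a separate approval procedure". Part B allows a subject to be told only for medical reasons and with the principal investigator's approval.
- **Same section, item (5).** Just before fascia closure, "each institution will notify the screening number to KGOG by phone and check the randomization result by phone as well". The site then receives the pair of screening and randomization numbers "so that the institution can input data on the eCRF".

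No separate hernia assessor, mandatory imaging or adjudication is described.

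**The concern.** Item (6) relies on one measure to shield the examiner: the allocation sits on the CRF and not in the medical record. Item (7) A then opens the CRF to the investigators at every site. The measure works only if the examiner does not look, and nothing in the protocol requires that.

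The endpoint is one where knowledge of the arm can matter. A physical examination needs judgment, and the same investigator decides whether to consult imaging or order another test. Knowing the suture could affect the call, the decision to test, or both. If the calls differed by arm for that reason, the primary comparison would carry detection bias that the analysis cannot remove. A report repeating the observation table would also claim a blinding that the access rule does not secure.

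**Working it through.** **1. Which allocation does item (7) A open?** The drain result is already disclosed under item (6) B. The lead-in to item (7) covers undisclosed results, so it can only mean the SS-PDS allocation, the one that defines the primary comparison.

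**2. Are there limits on access?** For subjects, item (7) B sets two: a medical reason and approval. For investigators, item (7) A sets none: no approval, no date, no exception for the Year 1 examiner. The controlled route exists in the protocol but does not apply to those who make the primary diagnosis.

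**3. Are there other routes to the allocation?** The operating team is told in words during surgery. Sites enter data in the same eCRF. Suture length is a collected item, and the two products come in 45 cm and 90 cm lengths, so that field may be a partial cue.

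**4. How many events carry the result?** Target Sample Size and Calculation Rationale gives 0.13 v 0.03, one-sided alpha 0.05, power 0.8, drop-out 0.06 and 87 per arm. The formula is not named, but the arcsine method reproduces the figure:

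- h = 2·arcsin√0.13 − 2·arcsin√0.03 = 0.3896
- n = 2·((1.6449 + 0.8416)/0.3896)² = 81.5 per arm
- 81.5/0.94 = 86.7, rounded up to 87

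Taking 82 evaluable per arm, the expected hernias are 82 × 0.13 = 10.7 and 82 × 0.03 = 2.5, about 13 in all.

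**5. How sensitive is the test to single calls?** With a and b hernias among 82 per arm and p̄ = (a + b)/164, the uncorrected statistic is z = ((a − b)/82) / √(2·p̄·(1 − p̄)/82). The protocol allows chi-square or Fisher's exact test. It states one-sided alpha for the sample size and gives no sidedness for the analysis.

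| Split | z | Chi-square, two-sided p | Chi-square, one-sided p | Fisher, one-sided p |
|---|---|---|---|---|
| 11 v 2 (13 events) | 2.601 | 0.009 | 0.005 | 0.009 |
| 10 v 3 | 2.023 | 0.043 | 0.022 | 0.040 |
| 9 v 4 | 1.445 | 0.148 | 0.074 | 0.123 |
| 11 v 3 (14 events) | 2.236 | 0.025 | 0.013 | 0.024 |
| 10 v 4 | 1.677 | 0.094 | 0.047 | 0.080 |

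From 11 v 2, one changed call in each arm leaves p below 0.05 in all three columns, and two in each arm lift it above 0.05 in all three. From 11 v 3, one changed call in each arm is enough on two-sided chi-square or one-sided Fisher, but not on one-sided chi-square.

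**6. An illustration with an assumed bias.** Suppose the true incidence is 0.13 in both arms, 81 per arm are evaluable, and a share m of hernias is missed in the SS-PDS arm only. The observed difference is d = 0.13·m. The chance of one-sided p < 0.05 is Φ((d − 1.645·se₀)/se₁), with se₀ the pooled and se₁ the unpooled standard error. It is 5.0% for m = 0, 8.2% for 10%, 12.9% for 20%, 19.6% for 30% and 28.7% for 40%. Both m and its direction are assumptions; the documents give neither.

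**The case against.** The best defence is that item (7) A only permits looking, while the observation table states the intended conduct. A reader might infer that the two statements cannot both be true. That goes too far: an investigator who never opens the field remains blinded, unless that investigator was at the closure. The defect is that the blinding is not enforced. The protocol also limits casual unblinding: investigators are not reminded of the arm, subjects are not told, and imaging or a further test is available in doubtful cases. These points stand, but they fall short of the blinding that the table states.

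A reader might also infer that the surgeon or the person who checked the CRF makes the Year 1 call. The protocol says only that investigators do so; it neither requires nor excludes that overlap.

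A third tempting inference is that one changed call in each arm overturns the result. The table above does not support this as a general statement: it depends on the starting split, the test and the sidedness.

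Finally, investigators have duties that use the allocation. Causality Evaluation asks them to judge a relation to the suture, and Reporting Methods sets a 7-day duty for certain events in the SS-PDS arm. Shutting sites out of the field altogether would obstruct this. That objection is sound and shapes the fix.

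**Conclusion.** The point holds as a failure to secure a stated blinding. The access rule, the reason for keeping allocation off the medical record, and the Year 1 blinding statement need to be reconciled within the protocol; this is not a matter left to an SAP.

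The exposure matters because the endpoint is examination-based and events are few. On the protocol's rates and about 82 evaluable per arm, one or two differential calls per arm, depending on the split and the test, could move the primary result across 0.05. That rests on the design incidences being about right.

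The documents do not support a claim that bias will occur, that it would favour SS-PDS, or that it has any particular size. The false-positive figures above are conditional on an assumed share of missed hernias.

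**What to change.** Reconcile items (5) to (7) of Control Group Setting and Randomization with the Year 1 observation row, as follows.

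1. Replace the open permission in item (7) A with a restriction in the eCRF: whoever performs the Year 1 hernia examination cannot see the SS-PDS allocation, or revealing fields such as suture length, until the Year 1 hernia form is locked.
2. Where a site already has more than one investigator, have the examination done by one who took no part in the closure. Hiding a field cannot blind a surgeon who heard the allocation by phone.
3. Keep a logged access route for medical need and for the causality and expedited reporting duties.
4. Record on the hernia form whether the examiner was the surgeon or had accessed the allocation, and do not report such assessments as blinded.

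The cost is a change to eCRF user rights covering more than one field, a wording change, one extra logged step when the allocation is needed, and some examiner scheduling. Treatment, visits and sample size are unaffected.

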G) Infections and infestations: abdominal infection, bladder infection, catheter related infection, peritoneal infection, pharyngitis, stoma site infection, urinary tract infection, wound infection

H) Injury, poisoning and procedural complications: intraoperative gastrointestinal injury, intraoperative venous injury, intraoperative urinary injury, large intestinal anastomotic leak, postoperative hemorrhage, wound complication, wound dehiscence

I) Investigations: activated partial thromboplastin time prolonged, alanine aminotransferase increased, alkaline phosphatase increased, aspartate aminotransferase increased, platelet count decreased, urine output decreased, weight gain, weight loss

J) Metabolism and nutrition disorders: anorexia, dehydration

K) Musculoskeletal and connective tissue disorders: back pain, flank pain, myalgia, neck pain

L) Psychiatric disorders: anxiety, delirium, insomnia

M) Renal and urinary disorders: hematuria, proteinuria, urinary frequency, urinary incontinence, urinary retention, urinary urgency

N) Reproductive system and breast disorders: menorrhagia, irregular menstruation, pelvic pain, vaginal discharge, vaginal dryness, vaginal hemorrhage

O) Respiratory, thoracic and mediastinal disorders: atelectasis, cough, dyspnea, hypoxia, pleural effusion, sore throat

P) Skin and subcutaneous tissue disorders: alopecia, pruritus, purpura, urticarial

Q) Vascular disorders: flushing, hot flashes, phlebitis, thromboembolic event

B. Side effects/risks from using barbed suture and countermeasures

A) Side effects/risks

Barbed suture has been used for various soft-tissue closures since years ago. SS-PDS is approved to be used for abdominal fascia closure. However, there are little clinical experience of using SS-PDS for abdominal fascia closure. Potential side effects/risks would include increased incisional hernia, surgical site infections, wound dehiscence and pain but increase is not expected.

B) Countermeasures

When the 10th subject is allocated to the A+B arm and completes his/her week 4 visit, an evaluation will be performed on 10 subjects in A+B arm for surgical site infections, wound dehiscence and incidence, types and grades of other adverse events. Evaluation results will be reported to IRB. If incidence, types, and grades of adverse events are judged to exceed the usual range, possible measures including trial discontinuation will be considered.

C. Side effects/risks from using subcutaneous drain and countermeasures

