**(1) Discontinuation**

A. The principal investigator can stop the study if it is judged that SS-PDS’s safety is low. Discontinuation of the trial can be considered when serious adverse events occurred from the interim analysis results.

B. The principal investigator can stop the trial if recommended by IRB.

C. The principal investigator can stop the trial if it is impossible to carry out the trial properly.

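### The only planned interim analysis of SS-PDS safety is an uncontrolled look at 10 patients with no defined benchmark, and the later 88-patient look does not compare the suture arms

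*Protocol*

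**What the plan says.** Control Group Setting and Randomization, (8) Interim Analysis, part A, sets an initial safety review in which "an evaluation will be performed on 10 subjects in A+B arm" for surgical site infection, wound dehiscence and other adverse events. The results go to the IRB, and the decision rule is: "If incidence, types, and grades of adverse events are judged to exceed the usual range, possible measures including trial discontinuation will be considered". Nothing in the protocol defines the range or names a C+D comparator.

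Benefits for and Risks to Subjects, (1) B, repeats this review as the countermeasure for the risks of the barbed suture. It concedes: "However, there are little clinical experience of using SS-PDS for abdominal fascia closure". It lists the harms in view: "Potential side effects/risks would include increased incisional hernia, surgical site infections, wound dehiscence and pain but increase is not expected".

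Part B of (8) sets a second look: "An evaluation will be performed when the 44th subject of A+C arm and B+D arm, respectively, completes his/her week 4 visit". Its only test is wound dehiscence with drain against without drain.

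Other safety routes exist:
- Under Reporting Methods, serious, unpredicted and causally related events in the SS-PDS arm are reported within 7 days, and all adverse events are collected and reported to the IRBs once a year.
- Under Discontinuation, the principal investigator may stop if SS-PDS safety is judged low, or on IRB recommendation. The same section adds: "Discontinuation of the trial can be considered when serious adverse events occurred from the interim analysis results".

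**The concern.** The review has to judge a count out of 10 with neither a stated reference rate nor concurrent patients, although 1:1 randomisation should supply about 10 controls over the same period. A reader cannot tell which result would raise a concern and which would allay one.

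No later look fills the gap. At the drain interim, Week 4 visits will be complete for roughly 44 SS-PDS and 44 control patients, yet the plan splits them by drain only. Infection and dehiscence, two of the harms that the protocol itself names, are therefore not compared by suture until the trial ends, and most SS-PDS patients are treated after the single look.

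**Working it through.** **Inputs from the protocol.** First look: 10 A+B patients. Second look: 44 + 44 = 88 by drain. Allocation of sutures 1:1, so about 10 controls at the first look and about 44 per suture arm at the second (expected, not fixed). Total 174, enrolment 9 per month.

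**Assumption.** The protocol gives no Week 4 rate of infection or dehiscence, so background rates of 5%, 10%, 15% and 20% are used as a range.

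The protocol states no error rate or power for the 10-patient look, so there is no figure of its own to reproduce.

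**Step 1. What 0 events can exclude.** One-sided 95% upper limit = 1 − 0.05^(1/n).
- n = 10: 1 − 0.05^(1/10) = 25.9%
- n = 44: 1 − 0.05^(1/44) = 6.6%

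The chance of seeing no event at a true rate of 5% is 0.95^10 = 0.60 with 10 patients and 0.95^44 = 0.105 with 44.

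**Step 2. Power of 10 patients with the background rate taken as known.** For each background rate p0, take the smallest r with P(X ≥ r | 10, p0) ≤ 0.05. Power is P(X ≥ r | 10, p1), with p1 = 2·p0 or 3·p0.

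| p0 | r | attained size | doubling | tripling | true rate for 80% power |
|---|---|---|---|---|---|
| 5% | 3 | 1.2% | 7% | 18% | 38% |
| 10% | 4 | 1.3% | 12% | 35% | 48% |
| 15% | 4 | 5.0% | 35% | 73% | 48% |
| 20% | 5 | 3.3% | 37% | 83% | 58% |

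Loosening the rule to 10% changes only the first two rows, where power for a doubling becomes 26% and 32%.

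**Step 3. Suture arms compared, one-sided Fisher test at 0.05, exact power.**

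| p0 | 10 vs 10, doubling | 10 vs 10, tripling | 44 vs 44, doubling | 44 vs 44, tripling |
|---|---|---|---|---|
| 5% | 1% | 3% | 10% | 33% |
| 10% | 5% | 14% | 27% | 69% |
| 15% | 9% | 27% | 42% | 90% |
| 20% | 13% | 43% | 57% | 98% |

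The 10 vs 10 comparison has less power than Step 2, because the background rate is now estimated instead of assumed known. The 44 vs 44 comparison does better than Step 2 in every row, without needing an external rate. The gain is largest for a tripling at a background of 10%, where 35% becomes 69%.

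**Step 4. Timing at 9 per month.** Ten SS-PDS patients imply about 20 randomised. Four more weeks add about 9 × 28/30.4 = 8, giving about 28 at the first look and 174 − 28 = 146 after it. For the second look, 88 + 8 = 96 are randomised and 174 − 96 = 78 remain.

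**The case against.** The strongest reply is that part A is labelled an initial review and looks at types and grades as well as counts. It is an early check for gross or striking harm with a device that the protocol describes as approved for this use, and not a powered test. The number of looks and the choice of comparator are design choices, and the protocol does not contradict itself here. Review criteria may also sit in a document that is not shown. This stands as far as it goes, and it limits the point.

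A reader might infer three stronger things that the documents do not support:

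- **That nothing else watches SS-PDS safety.** Expedited reports, yearly reports, monthly data monitoring and an open power to stop are all written in, and stopping does not require an interim result. None of them compares the suture arms, however. The 7-day route also covers unpredicted events only, while the protocol's list of predictable events includes wound infection and wound dehiscence.
- **That the look cannot detect harm.** It can detect true event rates of about 40% to 60%, or a single alarming case.
- **That concurrent controls or the 88-patient look would cure the problem.** Ten against ten is weaker than the single-arm rule, and 44 against 44 remains underpowered for a doubling. By then about 96 of 174 patients have been randomised.

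It would also be wrong to state that this population has a high wound-event rate. The protocol gives no such figure.

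**Conclusion.** The point holds in a limited form. The one planned interim analysis of SS-PDS safety is uncontrolled, has 10 patients and rests on an undefined benchmark. The planned look at 88 patients leaves the suture question out. The first look has little power for anything short of gross harm: 7% to 37% for a doubling. A suture comparison at the second look would raise this to 10% to 57%, and from 18% to 83% up to 33% to 98% for a tripling.

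These figures rest on assumed background rates of 5% to 20%, a one-sided 5% criterion that the protocol does not set, and near-equal suture arms at the second look. The case for change is that randomised controls would replace an unstated reference while about 78 patients are still to be randomised. It is not that the trial would then have a well-powered safety test.

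**What to change.** In (8) B, when 44 patients per drain group have completed Week 4, also tabulate infection by type, dehiscence and other adverse events for A+B against C+D, and report the table to the IRB. Include no hernia data and no efficacy test.

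In (8) A, and where it is repeated under Benefits for and Risks to Subjects, show the C+D patients who have completed Week 4 by the same date beside the 10 A+B patients. Name them as the reference in place of the usual range, and say that the table is context and not a powered test.

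The cost is one table at each of two analyses already planned, with no extra patients or visits. Part B now names dehiscence only, so infection and other adverse event data must also be checked and extracted at that time. The other downside is that whoever prepares the tables sees Week 4 safety by suture arm. The data centre should prepare them, and they should not go to the investigators who diagnose hernia. The added masking risk is small, because (7) A of the same section already lets investigators view allocation in the CRF without separate approval. Since the IRB can recommend stopping, the result can be acted on without circulating the table more widely.
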